#### 6.5.2.1 SAFETY MEASURES DURING IVT ADMINISTRATION

Patient must be closely monitored during study treatment administration for signs and symptoms of intracranial and/or extracranial bleeding and other potential complications.

One of the most dangerous complications of intravenous thrombolysis treatment is intracranial bleeding. According to SITS-MOST Register, a clinical deterioration of  $\geq 4$  points in NIHSS assessment of stroke severity associated with presence in neuroimaging examination of PH2 type bleeding (parenchymal haemorrhage type 2) according to ECCASS II classification is indicative of secondary symptomatic haemorrhagic transformation (symptomatic Intracranial Haemorrhage, sICH).

In the event of a suspected acute intracranial bleeding during the intravenous administration of thrombolytic treatment (i.e., when the patient experienced a severe headache, a sharp increase in blood pressure, nausea, vomiting, aggravation of an existing neurological deficit) - the infusion of rtPA should be stopped immediately and an urgent additional neuroimaging examination (head CT) should be performed.

In case of suspicion of other types of bleeding (to other areas of the body) - urgent imaging and laboratory diagnostics should be performed and applicable guidelines should be followed.

Similarly, in the event of a suspected new thromboembolic incident - urgent neuroimaging diagnostics should be performed, and applicable clinical guidelines should be followed.

For ECASS II classification of haemorrhagic transformation please refer to [Section 9.1.3.3](#).

---

#### 6.5.3 VISIT 2 (DAY 2) – POST-TREATMENT FOLLOW-UP 1

The following examinations and procedures should be performed at Visit 2:

1. Vital signs (BP and HR).
2. Signs and symptoms of infection(s).
3. Neurologic examination based on National Institutes of Health Stroke Scale (NIHSS).
4. Collecting blood sample for the following tests:
  - Coagulation parameters: INR, APTT, fibrinogen
  - Complete blood count (CBC) with platelet count
  - Blood glucose concentration
  - Biochemistry panel including electrolytes, serum creatinine (eGFR), CRP
  - Troponin I concentration
  - Transaminases (AlAT, AspAT) and bilirubin
  - Albumin.
5. Brain imaging: contrast-free CT scan (or MRI).
6. Review of concomitant medications.
7. DUS of extracranial / intracranial arteries (if not done before).

NOTE 1: The test should be performed at least once during hospitalization (V0-V3).

8. Echocardiography if not done before). NOTE 1: The test should be performed at least once during hospitalization (V0-V3).
9. Review of safety endpoints:
  - 1) any symptomatic intracranial haemorrhage (sICH),
  - 2) any life threatening extracranial bleeding,
  - 3) recurrent or new acute thromboembolic stroke,
  - 4) any life threatening thromboembolic complications,
  - 5) any significant allergic reactions assumed to be related with the administered substances (antidotes, rtPA).

The patient must be closely monitored, and any AEs/ Ars must be recorded in the patient's medical record and in the eCRF.

---

#### 6.5.4 VISIT 3 (DAY 7) – POST-TREATMENT FOLLOW-UP 2

The following assessments / procedures shall be carried out on day 7 ( $\pm$  1 day [=24 hours]) after the acute phase study treatment:

1. Vital signs (BP and HR).
2. Signs and symptoms of infection(s).
3. Performance status assessments including:
  - a. patient's neurological status using NIHSS scale
  - b. patient's performance using mRS
  - c. patient evaluation using Barthel scales, MoCA, IQCODE and HADS questionnaires.
4. Collecting blood sample for the following tests:
  - Coagulation parameters: INR, APTT, fibrinogen
  - Complete blood count (CBC) with platelet count
  - Biochemistry panel: CRP
  - BNP/ NT-proBNP.
5. MRI of the head/brain.
6. Review of adverse events.
7. Review of safety endpoints:
  - 1) any symptomatic intracranial haemorrhage (sICH),
  - 2) any life threatening extracranial bleeding,
  - 3) recurrent or new acute thromboembolic stroke,
  - 4) any life threatening thromboembolic complications,
  - 5) any significant allergic reactions assumed to be related with the administered substances (antidotes, rtPA).
8. Review of concomitant medications.
9. DUS of extracranial / intracranial arteries (if not done before).

NOTE 1: The test should be performed at least once during hospitalization (V0-V3).
10. Echocardiography if not done before).

NOTE 1: The test should be performed at least once during hospitalization (V0-V3).

Data should be entered on the eCRF.

---

#### 6.5.5 VISIT 4 (DAY 30) – POST-TREATMENT FOLLOW-UP 3

The patient's assessment should be carried out with patient and/or caregiver. A visit to the clinic is allowed but can be conducted as a phone call.

The following assessments shall be carried out / information obtained on day 30 ( $\pm 2$  days) after the acute phase study treatment:

1. Patient's performance using mRS scale.
2. Patient's whereabouts (own home / family care, care home, hospital, others).
3. Review of adverse events.
4. Review of concomitant medications.
5. Review of safety endpoints:
  - 1) any symptomatic intracranial haemorrhage (sICH),
  - 2) any life threatening extracranial bleeding,
  - 3) recurrent or new acute thromboembolic stroke,
  - 4) any life threatening thromboembolic complications,
  - 5) any significant allergic reactions assumed to be related with the administered substances (antidotes, rtPA).

Phone call contacts must be documented in patient medical records and entered on eCRF accordingly.

---

#### 6.5.6 VISIT 5 (DAY 90) – END OF STUDY

The patient's assessment should be carried out with patient and/or caregiver. A visit to the clinic is strongly preferred but in exceptional situations can be conducted as a phone call (the reasons for not visiting the center (hospital) should be given in detail).

The following assessments shall be carried out / information obtained on day 90 ( $\pm 3$  days) after the acute phase study treatment (End of Study Visit):

1. Vital signs (BP and HR).
2. Signs and symptoms of infection(s).
3. Performance status assessments including:
  - a. Patient's neurological status with the NIHSS scale
  - b. Patient's performance using mRS
  - c. Patient evaluation using Barthel scales, MoCA and HADS questionnaires.
4. Review of adverse events.
5. Review of safety endpoints:
  - 1) any symptomatic intracranial haemorrhage (sICH),
  - 2) any life threatening extracranial bleeding,
  - 3) recurrent or new acute thromboembolic stroke,
  - 4) any life threatening thromboembolic complications,
  - 5) any significant allergic reactions assumed to be related with the administered substances (antidotes, rtPA).
6. Review of concomitant medications.

Phone call contacts must be documented in patient medical records and entered on eCRF accordingly.

---

#### 6.5.7 UNSCHEDULED VISIT

Additional (unscheduled) visits may take place between visits scheduled in the protocol to assess the occurrence and effects of adverse reactions or endpoints, as well as when a patient withdraws from the study.

## 7 STUDY INTERVENTION

### 7.1 STUDY INTERVENTION(S) ADMINISTRATION

#### 7.1.1 STUDY INTERVENTION DESCRIPTION

Patients with AIS on NOAC (dabigatran, apixaban or rivaroxaban) who are eligible for the study will receive reperfusion thrombolytic treatment with intravenous rtPA (alteplase) following administration of the specific reversal agent / antidote (idarucizumab for dabigatran; andexanet alpha for apixaban and rivaroxaban).

Study intervention is defined as sequential therapy including administration of NOAC specific neutralising (reversal) agent / antidote (idarucizumab or andexanet) and rtPA (alteplase) or corresponding placebo.

Placebo to antidote and rtPA (0.9% NaCl solution) will be prepared *ex tempore* immediately after randomisation.

All components of the study intervention (combination / sequential therapy) are commercially available medicinal products. Dosage and administration will follow the current local prescribing information.

#### 7.1.2 DOSING AND ADMINISTRATION

All components of the study intervention (combination / sequential therapy) are commercially available medicinal products. Dosage and administration will follow the current local prescribing information.

In the STROACT study, rtPA (both bolus and infusion) should be administered to a vein of the arm contralateral to the ischemic lesion (commonly paretic), whereas antidote (idarucizumab or both bolus and infusion of andexanet alfa) to a vein of the arm ipsilateral to the ischemic lesion. For many years of the use of rtPA for ischemic stroke, there have been no major or significant reports showing any differences between action of rtPA administered to ipsi- and contra-lateral arms (that might be potentially caused by some processes like for example local autonomic disturbances), whereas data on such potential associations for both antidotes are poor.

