| Study treatment group                      | Antidote and rtPA dosing and administration                                                                                                                                                                                                                                                                                                                                                                                                                                                                                                                                                                                                                                                                                                                    |
|--------------------------------------------|----------------------------------------------------------------------------------------------------------------------------------------------------------------------------------------------------------------------------------------------------------------------------------------------------------------------------------------------------------------------------------------------------------------------------------------------------------------------------------------------------------------------------------------------------------------------------------------------------------------------------------------------------------------------------------------------------------------------------------------------------------------|
| Study group A
(patients on dabigatran)  | 
 
Antidote
Idarucizumab at a dose of 5 g (2 vials of 2.5 g/50 mL) will be administered intravenously as two consecutive infusions or over 5 to 10 minutes each, or as a rapid intravenous injection (bolus).
 
Reperfusion thrombolytic treatment
Alteplase at a dose of 0.9 mg/kg of body weight (maximum 90 mg) administered intravenously; 10% of the calculated dose in a rapid intravenous injection (bolus) within 1-2 minutes, and 90% of the calculated dose in an intravenous infusion over 1 hour (syringe pump).
 
                                                                                                                                                       |

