| Study group B
(patients on apixaban)    | 
 
Antidote
Andexanet alpha will be administered as an intravenous bolus a: 
 
Low dose: target infusion rate of 30 mg/min for approximately 14 minutes (up to the dose of 400 mg), followed by a continuous infusion at 4 mg/min for 120 min
 
High dose: target infusion rate of 30 mg/min for approximately 27 minutes (up to the dose of 800 mg), followed by a continuous infusion at 8 mg/min for 120 min (administration in a syringe pump after reconstitution of all required vials).
 
 
 
Reperfusion thrombolytic treatment
Alteplase (rtPA) - the same dosing and administration instructions as in study group A.
 
 |
| Study group C
(patients on rivaroxaban) | 
 
Antidote
Andexanet alpha - the same dosing and administration instructions as for the study group B.
 
Reperfusion thrombolytic treatment
Alteplase (rtPA) - the same dosing and administration instructions as for the study group A, and B.
 
                                                                                                                                                                                                                                                                                                                                                                                                                                   |

Dosing of andexanet alfa in the STROACT study (low dose or high dose) will be guided by anti-Xa activity (for either apixaban or rivaroxaban) and the time from the last intake of apixaban or rivaroxaban dose before AIS (please refer to the table below).

| Anti-Xa activity    | Time form the last dose of apixaban or rivaroxaban |           |           |
|---------------------|----------------------------------------------------|-----------|-----------|
|                     | <4h or unknown                                     | 4-8h      | ≥8h       |
| >50ng/mL, <100ng/mL | High dose                                          | Low dose  | Low dose  |
| ≥100ng/mL           | High dose                                          | High dose | High dose |

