## 4.4 JUSTIFICATION FOR DOSE

Study intervention in the STROACT study is defined as a sequential intravenous administration of NOAC-specific reversal agent / antidote (idarucizumab or andexanet) and rtPA (alteplase) or corresponding placebo.

All components of the study intervention (combination / sequential therapy) are commercially available medicinal products. Dosage and administration will follow the current product SmPC /local prescribing information. For andexanet alfa dosing two levels of anti-Xa activity and time from the last dose will guide selection of low or high dose of andexanet alfa in the sequential therapy.

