### 4.4.3 ANDEXANET ALFA

Andexanet alfa is a specific, fast-acting, reversal agent for apixaban and rivaroxaban anticoagulant activity and will be administered in according to the standard dosing instructions approved for emergency surgery/urgent procedures, adjusted for results of anti-Xa activity assessed at admission

and information about the last dose taken. Current dosing instructions for andexanet alfa refer to the dose of apixaban or rivaroxaban taken and time from the last dose (Ondexxya SmPC, 2020)., however availability of assays to determine specific NOAC drug concentrations correlating with anti-Xa activity and knowledge of PK/PD profile of apixaban and rivaroxaban can support optimal clinical decision-making on dosing of andexanet alfa before starting IVT with rtPA in order to minimise the potential thromboembolic risk associated with andexanet alfa administration.

Selection of andexanet alfa dose (low or high dose) in the STROACT study will be guided by anti-Xa activity level and the time from the last intake of apixaban or rivaroxaban dose before AIS (please refer to [Table 1](#) below).

**Table 1** Dosing of andexanet alfa in the STROACT study (low and high dose).

| Anti-Xa activity level | Time form the last dose of apixaban or rivaroxaban |           |           |
|------------------------|----------------------------------------------------|-----------|-----------|
|                        | <4h or unknown                                     | 4-8h      | ≥8h       |
| >50ng/mL, <100ng/mL    | High dose                                          | Low dose  | Low dose  |
| ≥100ng/mL              | High dose                                          | High dose | High dose |

For detailed information on dosage and administration please refer to [Section 7.1.2](#).

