#### 6.5.2 VISIT 1 (DAY 1) – STUDY TREATMENT ADMINISTRATION

After obtaining lab results of anti-IIa activity for dabigatran (or dabigatran concentration itself) or anti-Xa for rivaroxaban or apixaban confirming high anticoagulation activity (>50 ng/ml) study treatment can be administered. However, in patients on dabigatran, it is possible to enrol such a subject into the study based solely on a patient's or witness' report on the last intake of the anticoagulant ie, when it was administered within the last 24 hours preceding initiation of the study treatment. In these situations it is obligatory to collect and store blood for post-hoc anti-IIa testing. The procedure is described in the Laboratory Manual. Blinded study treatment will be dispensed by unblinded personnel according to the treatment allocation instruction received via eCRF notification (see [Section 6.4.3](#)).

Study treatment will be administered according to the study protocol as a as sequential intravenous administration of NOAC-specific antidote (idarucizumab or andexanet) and tPA (alteplase) or corresponding placebos for each of the study treatment components. **Please refer to dosing instructions in [Section 7.1.2](#).**

1. Vital signs. BP and HR should be monitored and recorded:
  - in the 1. hour
  - in the 2. hour
  - in the 3. hour
  - in the 4. hour
  - in the 5. hour
  - in the 6. hourfrom the start of study treatment administration.
2. Two consecutive blood sample for anti-Xa activity for rivaroxaban or apixaban must be collected:
  - after completion of antidote (or antidote placebo) bolus injection
  - after completion of rtPA (or corresponding placebo) infusion.

Measurements anti-IIa 2nd and 3rd are only facultative.

The start and completion time of each study treatment component, time of blood sample collection for assessment of anti-IIa/Xa activity must be recorded in patient medical records and in eCRF.

3. Review of concomitant medications.
4. DUS of extracranial / intracranial arteries (if not done before).  
NOTE 1: The test should be performed at least once during hospitalization (V0-V3).
5. Echocardiography if not done before).  
NOTE 1: The test should be performed at least once during hospitalization (V0-V3).
6. Collection of blood sample for measure of blood glucose concentration. Obligatory only in cases where the screening value was beyond that defined in inclusion/exclusion criteria.
7. ECG (if not done before).  

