**Table 2 Study groups and investigational treatment.**

| Study treatment group                      | Antidote and rtPA dosing and administration                                                                                                                                                                                                                                                                                                                                                                                                                                                                                                                                                                                                                                                                                   |
|--------------------------------------------|-------------------------------------------------------------------------------------------------------------------------------------------------------------------------------------------------------------------------------------------------------------------------------------------------------------------------------------------------------------------------------------------------------------------------------------------------------------------------------------------------------------------------------------------------------------------------------------------------------------------------------------------------------------------------------------------------------------------------------|
| Study group A
(patients on dabigatran)  | 
1. Antidote
Idarucizumab at a dose of 5 g (2 vials of 2.5 g/50 mL) will be administered intravenously as two consecutive infusions or as a rapid intravenous injection (bolus) over 5 to 10 minutes each.
 
2. Reperfusion thrombolytic treatment
Alteplase (rtPA) administered intravenously at a dose of 0.9 mg/kg (maximum 90 mg), of which 10% of the calculated dose in a rapid intravenous injection (bolus) within 1-2 minutes, and the remainder, i.e. 90% of the calculated dose in an intravenous infusion within 1 hour (syringe pump).
                                                                                                                                          |

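### Section 7.1.2, the section sites are sent to for dosing, says dosing follows the local prescribing information and omits the trial's own andexanet selection rule, which Section 4.4.3 says uses different inputs

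*Protocol*

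**What the plan says.** **What governs dosing.** Protocol 7.1.2 says of all components of the intervention: "Dosage and administration will follow the current local prescribing information". The same sentence stands in 1.1.6 and 7.1.1, and 4.4 has a near-identical one.

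**Where readers are sent.** At Visit 1, Section 6.5.2 tells staff "Please refer to dosing instructions in" Section 7.1.2. Sections 4.4.1, 4.4.2 and 4.4.3 also refer there for detail.

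**What 7.1.2 gives for andexanet.** Table 2 sets out a low and a high regimen. It has no selection rule and no reference to Table 1.

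**The trial's selection rule.** Section 1.1.6 says the level "will be guided by anti-Xa activity (for either apixaban or rivaroxaban) and the time from the last intake" and prints a table. Section 4.4 says "two levels of anti-Xa activity and time from the last dose will guide selection of low or high dose of andexanet alfa". Section 4.4.3 says "Selection of andexanet alfa dose (low or high dose) in the STROACT study will be guided by anti-Xa activity level" and time since intake, and prints the same grid as Table 1.

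**What the protocol says about the existing instructions.** Section 4.4.3: "Current dosing instructions for andexanet alfa refer to the dose of apixaban or rivaroxaban taken and time from the last dose".

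**Idarucizumab.** Section 1.1.6 has "as two consecutive infusions or over 5 to 10 minutes each, or as a rapid intravenous injection (bolus"). Table 2 has "as two consecutive infusions or as a rapid intravenous injection (bolus) over 5 to 10 minutes each".

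**The concern.** The section named as the source for dosing gives one governing statement, the prescribing information. By the protocol's own account, that is the basis the trial departs from when choosing the andexanet level. A reader who goes straight from Visit 1 to 7.1.2 meets two regimens and is told to follow a source whose selector differs from the trial's.

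Uniform delivery of the experimental treatment in groups B and C is at stake, together with safety. Section 4.4.3 justifies the anti-Xa rule partly by thromboembolic risk, Section 2.3.2 says there are no empirical data on andexanet followed by rtPA, and Section 1.1.10.2 plans a safety look after the first six patients in each of these groups. If the level was chosen by different rules at different sites, those early data would be harder to read.

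**Working it through.** No statistical figure is in dispute, so the check is a comparison of texts plus simple dose arithmetic.

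**1. Do the regimens themselves agree?** Yes. Section 1.1.6 and Table 2 give the same andexanet amounts and rates.

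- Low bolus: 400 mg / 30 mg per min = 13.3 min (stated as about 14).
- High bolus: 800 mg / 30 mg per min = 26.7 min (stated as about 27).

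**2. How far apart are the levels?** Total = bolus + infusion rate × 120 min.

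- Low: 400 + 4 × 120 = 880 mg.
- High: 800 + 8 × 120 = 1760 mg.
- Ratio: 1760 / 880 = 2.

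**3. Which inputs select the level?**

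| Source | Inputs |
|---|---|
| 1.1.6, 4.4, 4.4.3 (trial rule) | Anti-Xa level (above 50 and below 100, or at least 100 ng/mL) and time since last intake |
| Current instructions, as 4.4.3 describes them | Dose of apixaban or rivaroxaban taken and time since last dose |
| 7.1.2 with Table 2 | None stated; the prescribing information is said to apply |

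**4. Can the two rules always agree?** Take two illustrative patients on the same anticoagulant at the same dose, both equally long after intake and within the 4-8 h column. One measures 60 ng/mL and the other 150 ng/mL (assumed values). Table 1 assigns low to the first and high to the second. A rule that uses only the dose taken and the time cannot tell them apart, so it gives both the same level and must differ from Table 1 for one of them. This assumes that the two inputs named in 4.4.3 are the only ones. The protocol does not reproduce the instructions' cut-offs, so the frequency of disagreement cannot be worked out.

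**5. How many patients fall under the wording?** At most all actively treated patients in groups B and C: 2 × 46 = 92 at the calculated minimum (11.3), or 2 × 50 = 100 at the approximate enrolment in 1.1.9. This counts those to whom the text applies, not those whose dose would change.

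**6. Idarucizumab.** Both passages give 2 × 2.5 g = 5 g. Section 1.1.6 places the 5 to 10 minutes with the infusions and gives the bolus no duration. In Table 2 the same duration follows the bolus. The amounts agree; only the wording on mode and duration differs.

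**The case against.** The best defence is that the protocol, read as a whole, has one andexanet rule. The grids in 1.1.6 and 4.4.3 are identical, and no competing table is printed anywhere. In 1.1.6 and 4.4 the prescribing-information sentence is followed by the trial-specific rule. Section 4.4.3 describes standard instructions adjusted for anti-Xa and explains why. The natural reading is the label by default, with the stated exception for the andexanet level. The referral in 4.4.3 comes directly after Table 1, so that reader has just seen the rule. For andexanet, only the Visit 1 referral bypasses it.

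Most of this stands, and it limits the point. It does not clear 7.1.2, where the general sentence appears without the exception.

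A reader might infer more, and the documents do not support it:

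- **That different levels at the same anti-Xa value show a fault.** Table 1 itself does this: above 50 and below 100 ng/mL, intake under 4 h ago or at an unknown time gives high, and 4-8 h gives low.
- **That no standard exists for calling a dose a deviation.** Table 1 is a usable standard, and Section 7.4 requires doses and timing to be recorded and departures reviewed.
- **That a dose-level efficacy analysis is compromised.** Section 11.5.2.1 compares active treatment with placebo within each arm; the protocol specifies no analysis by andexanet level.
- **That 7.1.2 conflicts with all of 1.1.6.** Section 1.1.6 carries the same general sentence; the conflict is with its selection table.

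**Conclusion.** The point holds as an inconsistency in the operative dosing section that should be corrected. Section 7.1.2 states a governing source which, on the protocol's own description, selects the andexanet level from different inputs than the trial rule, and it neither states nor points to that rule. A site using 7.1.2 alone could therefore choose the level by a different rule, and the two levels differ twofold in total (880 against 1760 mg).

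That gap is the distance between the planned levels, not a measured effect of the wording. The discordant share is not derivable, and there is no evidence that any patient was dosed by the wrong rule. The conclusion relies on 4.4.3's account of the current instructions and on no outside source. The idarucizumab mismatch is minor: it affects group A wording only, at an unchanged 5 g total. Which text is correct is for the sponsor to decide; no view is taken here on any dose or rule.

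**What to change.** 1. Reconcile 1.1.6, 4.4, 7.1.1 and 7.1.2 so that 7.1.2 states, or refers explicitly to, the single andexanet selection rule the sponsor confirms.
2. Limit the prescribing-information sentence, wherever it appears, to the matters it is meant to govern.
3. For andexanet patients already treated, compare the recorded dose and timing (7.4), anti-Xa value (Visit 0), time of last intake (6.5.1) and anticoagulant dosage (7.6) to see which rule was applied. Where both rules give the same level, the record alone cannot tell them apart; ask the site.
4. Align the idarucizumab infusion and bolus wording in 1.1.6 and Table 2.

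The cost is a protocol wording amendment with its usual approval, a notice to sites and a short data check. Sample size and analysis are unaffected.
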